#### Secondary outcome measures

**Fugl-Meyer Assessment (FMA) scale for motor function** The FMA was developed as the first quantitative evaluative instrument for measuring sensorimotor stroke recovery, which includes an assessment of the upper extremity (UE, 66 points) and lower extremity (LE, 34 points). The motor domain has well-established reliability and validity as an indicator of motor impairment severity across different stroke recovery time points
[20].

**The mini-mental state examination (MMSE) and Montreal cognitive assessment (MoCA) for cognitive function** The MMSE, first introduced by Folstein and colleagues in 1975
[21], has become a standard tool for cognitive assessment in the clinical setting. It is a 10-minute bedside measure of impaired thinking in undeveloped, uneducated, diseased, or very old populations. The summed score of the individual items indicates the current severity of cognitive impairment
[22]. However, there are many difficulties in detecting early dementia with the MMSE. Most individuals meet clinical criteria for mild cognitive impairment (MCI), but have scores above 26 on the MMSE, which is within the range for normal elderly individuals. To address this problem the MoCA was developed as a tool to screen patients who present with mild cognitive complaints and usually perform in the normal range on the MMSE
[23]. The MoCA is used as a screening tool for MCI in baseline assessment in our study.

**Video-fluoroscopic swallowing study (VFSS) for swallowing ability evaluation** The functional dysphagia scale is based on the VFSS in stroke patients, which is a sensitive and specific method for quantifying the severity of dysphagia
[24,25].

**Incidence of adverse events** The subjects will be requested to voluntarily report information about adverse events. All adverse events happening during the trial will be recorded, such as pallor, sweating or dizziness, fainting during acupuncture treatment, bleeding, local hematoma, unbearable prickling, retained needle after treatment, and continuous severe pain more than one hour after acupuncture. The researcher will confirm the occurrence of adverse events and record all details such as the date of occurrence, time, degree, measurement related to the treatment, and causal relationship with the treatment. Serious adverse events will be reported to the principal investigator immediately.

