**Methods/Design:**

In a prospective trial involving three hospitals in the Zhejiang Province (China) 250 patients with a recent (less than 1 week previous) episode of ischemic stroke will be included. Patients will be randomized into two groups: an acupuncture group given scalp acupuncture and electroacupuncture, and a control group given no acupuncture. Eighteen treatment sessions will be performed over a three-week period. The primary outcome will be measured by changes in the National Institutes of Health Stroke Scale score at the one, three, and four-week follow-up. Secondary outcome measures will be: 1) the Fugl-Meyer assessment scale for motor function; 2) the mini-mental state examination and Montreal cognitive assessment for cognitive function; 3) the video-fluoroscopic swallowing study for swallowing ability; and 4) the incidence of adverse events.

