### Exclusion criteria

Patients who received thrombolytic therapy or who participated in other clinical trials within last three months are not included. Patients who suffered from serious heart,liver,kidney related diseases, blood coagulation dysfunction, or severe mental disorders will not be included. Women who are pregnant or breast-feeding and patients with a severe cognitive impairment are also excluded.

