#### Baseline assessments

Baseline assessments will be conducted before randomization, including gender and age of patients, clinical syndrome (left or right hemiplegia), diseased location and size, NIHSS and Fugl-Meyer assessment (FMA) scores, cognitive impairment based on the Montreal cognitive assessment (MoCA), and swallowing disorder according to the standardized swallowing assessment.

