### Statistical analysis

All data will be analyzed by a blinded statistician using the SPSS(Statistical Product and Service Solutions) statistical package program (version 17.0, SPSS Inc., Chicago, Illinois, United States) at a separate location from the clinical research institute of Zhejiang Provincial Hospital of Chinese medicine. Baseline data will be collected and compared first. All patients randomized to each group are included in the analysis and the data analysis will be conducted using two-sided significance tests at the 5% significance level. The analysis of swallowing disorder and cognitive impairment will be made on the defined population of corresponding dysfunction in the baseline assessment. Different statistics are presented differently; for example, continuous variables will be expressed as mean ± SD, *t*-test will be used for comparisons of two independent samples, and non-parametric tests will be used for variables that do not follow a normal distribution. A *P* value of less than 0.05 (α value of 0.05) is considered to indicate statistical significance. A safety analysis will be performed by analyzing the frequency of adverse events suspected as related to the treatment. The data for adverse events are collected through the symptoms reported by the patients, and observations by a researcher at every visit.

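### The MoCA is named as a cognitive secondary outcome but described in the text only as a baseline screen, so it is unsettled which scale measures cognition after treatment

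*Protocol article*

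**What the plan says.** The abstract (Methods/Design) lists among the secondary outcomes "the mini-mental state examination and Montreal cognitive assessment for cognitive function". Under Secondary outcome measures, the heading of the cognitive paragraph names the same pair: "The mini-mental state examination (MMSE) and Montreal cognitive assessment (MoCA) for cognitive function". That paragraph then warns that the MMSE misses early impairment, because most people who meet criteria for mild cognitive impairment (MCI) "have scores above 26 on the MMSE, which is within the range for normal elderly individuals". It presents the MoCA as the answer to that problem and closes with "The MoCA is used as a screening tool for MCI in baseline assessment in our study".

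Baseline assessments uses the scale in the same way, recording "cognitive impairment based on the Montreal cognitive assessment (MoCA), and swallowing disorder according to the standardized swallowing assessment". That list is introduced by the word including. It names neither the MMSE nor the video-fluoroscopic swallowing study (VFSS). Exclusion criteria adds that "patients with a severe cognitive impairment are also excluded". Under Statistical analysis, the cognitive and swallowing comparisons "will be made on the defined population of corresponding dysfunction in the baseline assessment". The method named there for two groups is the t-test, or a non-parametric test where data are not normal. No covariate adjustment is mentioned.

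**The concern.** Which scale is the outcome belongs in the protocol, and here the answer depends on the line read. Two places make the MoCA an outcome. Two others give it only a baseline use, and none gives it a follow-up visit.

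The choice matters because the article itself says the two scales differ in sensitivity to mild impairment. Selecting patients on the more sensitive scale and following them on the less sensitive one could leave many with little room to improve, and a null result on cognition would then be hard to read. With two scales and no main one named, there is also room to emphasise whichever gives the better result.

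A related gap affects both functional domains. Patients are selected on one instrument (MoCA, standardized swallowing assessment), while another may carry the outcome (MMSE, VFSS) with no baseline stated on its own scale.

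**Working it through.** The plan has no numerical figure on this point. Its only sample size calculation is for the NIHSS, and it reproduces: a difference of 2, SD 5.0, two-sided 5% and 80% power give 99 per group against about 100 stated, and 100/(1 − 0.20) = 125. It says nothing about the cognitive or swallowing subgroups, so the check is a comparison of sections.

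**1. Role of the MoCA**

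| Place in the protocol article | Role given |
|---|---|
| Abstract, Methods/Design | Secondary outcome, with the MMSE |
| Secondary outcome measures, paragraph heading | Secondary outcome, with the MMSE |
| Secondary outcome measures, paragraph text | Baseline screen for MCI |
| Baseline assessments | Defines cognitive impairment before randomization |
| Any section | No MoCA stated after baseline |

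The conflict is therefore not simply abstract against methods. The cognitive paragraph disagrees with its own heading.

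**2. Who is analysed.** Statistical analysis restricts cognition to patients with that dysfunction at baseline, and Baseline assessments defines it by the MoCA. Severe impairment is excluded. The extra cognitive acupoints in the Acupuncture group section are for mild impairment. Together these point to a mainly mild subgroup, but moderate impairment is not expressly excluded.

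**3. Room on the MMSE if it stands alone.** The article does not state the scale's maximum; I assume 30. A whole-number score above 26 is then 27 to 30, so the largest possible gain is 30 − 27 = 3 points and the smallest is 30 − 30 = 0. The article says most people with MCI score there, not all. It gives no MMSE distribution for patients in their first week after stroke, so the share of the subgroup near the ceiling is unknown.

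**4. What a missing same-scale baseline costs.** Randomization keeps a comparison of post-treatment scores valid without any baseline value. Only precision is lost. With a linear covariate whose correlation with the outcome is ρ, the ANCOVA residual variance is roughly (1 − ρ²) times that of the unadjusted comparison. The covariate need not be on the outcome's own scale. Baseline MoCA can serve for a follow-up MoCA or MMSE, and the baseline standardized swallowing assessment can serve for the VFSS. Both are already collected. The article gives no ρ, and selecting on baseline MoCA narrows its range, so the gain cannot be stated and may be modest.

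**The case against.** The strongest reply is that one scale can be both screen and outcome. The closing sentence of the cognitive paragraph adds a screening use and does not withdraw the outcome use announced in the heading and the abstract. This stands in part. A reader might infer that the MMSE is the sole follow-up measure, but the article never says so. That reading is conditional on the text overriding the heading.

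Second, the remark about scores above 26 describes people with MCI in general, whereas this trial enrols patients two to seven days after stroke with NIHSS 4 to 24. That also stands. A ceiling is a reasonable worry here, not a demonstrated fact.

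Third, the baseline list is open, and a full schedule of instruments by visit is something a condensed article may leave out. So a reader may not conclude that the MMSE and VFSS are unmeasured at baseline, only that this is not stated. Nor does it follow that baseline adjustment is impossible, since suitable covariates are on the list.

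Fourth, a reader might add that these subgroups are underpowered. The article gives no subgroup size and no SD for either cognitive scale, and a small subgroup would limit any scale alike, so this is not an argument for one over the other.

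What the reply does not remove is the inconsistency. If the MoCA is repeated, the text misdescribes a secondary outcome. If it is not, the abstract and the heading do.

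**Conclusion.** The point holds as an inconsistency in a secondary outcome, with a conditional consequence. The article names the MoCA as an outcome in two places, gives it only a baseline role in the text, and places it at no later visit. If the text governs, cognition in a MoCA-selected subgroup without severe impairment would rest on a scale the article itself regards as weak in mild impairment. The possible gain is then 0 to 3 points for patients scoring above 26, assuming a maximum of 30. The fraction of patients affected is unknown.

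For the MMSE and VFSS, a same-scale baseline is not stated. The cost is precision, not validity. It would go too far to say that the aim of assessing cognition and swallowing cannot be met, because valid randomized comparisons remain. The primary NIHSS analysis is untouched.

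**What to change.** Align the abstract, Baseline assessments and Secondary outcome measures so that the MoCA is the main cognitive secondary outcome at the three-week visit, the time point the sample size section uses for the primary outcome. Make the MMSE supportive, and state at which visits each scale is given.

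For cognition in the baseline-impaired subgroup, replace the unadjusted t-test with ANCOVA on baseline MoCA. If the MoCA was not repeated, keep baseline MoCA as the covariate for the MMSE. Analyse the VFSS with the baseline standardized swallowing assessment as covariate, which needs no further imaging. Fix these choices before outcome data are compared by group.

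The wording and the covariates cost nothing. A follow-up MoCA costs one short bedside test per subgroup patient where it is not already done. Enrolment began on 1 March 2012 and completion was expected by the end of June 2014, with the article published on 8 June 2014. A test not done cannot be recovered for patients already followed up, so for them the fallback with baseline MoCA as covariate is what remains.

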### Interventions and comparison

The study is a randomized clinical trial carried out in three inpatient rehabilitation departments of three hospitals. Participants will be randomized to either the control or the acupuncture group. Both groups will receive conventional stroke rehabilitation care, which begins as soon as the diagnosis of stroke is established and life-threatening problems are under control. The basic rehabilitation care includes normal limb posture, passive motion with hemiplegia side, bedside rehabilitation (Bobath technique, overturning movement, bridge movement), and/or neuromuscular electrical stimulation, swallow training for dysphagia, and/or cognitive training for cognitive impairment. The rehabilitation program (including physiotherapy and occupational therapy for two hours per day, six days per week) of each participant will be developed by the rehabilitation team according to the investigator’s brochure. The acupuncture group will receive 30 additional minutes of acupuncture therapy for six days per week for three weeks (18 total sessions) during the inpatient stay.

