#### No acupuncture treatment group

Patients in the control group will receive conventional stroke rehabilitation care, which is the same as the acupuncture group. However, no acupuncture treatments will be given during the study period. They will be assessed at each visit.

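### Adverse events rest on voluntary report and visit observation in an open-label comparison, so capture is likely to be less complete in the control arm and in patients with language deficits

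*Protocol article*

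**What the plan says.** The abstract lists the incidence of adverse events among the secondary outcomes, and its background paragraph gives safety as an aim alongside efficacy.

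Collection is described in two places. Under Secondary outcome measures: "The subjects will be requested to voluntarily report information about adverse events". Under Statistical analysis: "The data for adverse events are collected through the symptoms reported by the patients, and observations by a researcher at every visit".

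The scope is broad and the list is illustrative: "All adverse events happening during the trial will be recorded, such as pallor, sweating or dizziness, fainting during acupuncture treatment, bleeding, local hematoma", continuing with "unbearable prickling, retained needle after treatment, and continuous severe pain more than one hour after acupuncture". The researcher then confirms each event and records its details, including a causality judgement.

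On controls, the section on the no-acupuncture group says "They will be assessed at each visit". Under Outcome assessment, both arms are examined at baseline, one week, the end of the three-week treatment and a final follow-up. Interventions and comparison gives the acupuncture arm 18 sessions of 30 minutes on top of rehabilitation that both arms receive for two hours a day, six days a week. Randomization and blinding tells patients that they will have rehabilitation with or without acupuncture, and states that acupuncturists cannot be blinded.

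**The concern.** Voluntary report depends on the patient having an occasion to speak, believing that the event matters, and being able to say so. The first two can differ by arm. Acupuncture patients have a further treatment contact six days a week, know that they are receiving the studied intervention, and are observed against examples drawn mainly from needling. Control patients have none of these prompts.

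The third varies with the stroke itself. Patients with an NIHSS score up to 24 are eligible, that scale scores language, and aphasia is not an exclusion.

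At stake is whether the between-arm incidence reflects harm or partly reflects who was more likely to be heard. Under-capture in controls would make acupuncture look less safe than it is. No later analysis can restore an event that was never elicited.

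**Working it through.** The article's only computed figure is the sample size, and this point does not depend on it. It reproduces: a difference of 2 points, SD 5.0, two-sided 5% and 80% power give 99 per group against a stated figure of about 100, and 100 / (1 − 0.20) = 125. I use 125 per arm below.

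**1. Contacts at which an event could surface, by arm.** Assume the shared rehabilitation runs for the same three weeks as acupuncture.
- Shared therapy days: 6 × 3 = 18 in each arm.
- Post-baseline assessments: 3 in each arm (week 1, week 3, final follow-up).
- Acupuncture sessions: 6 × 3 = 18 in one arm only.
- Totals: 18 + 3 + 18 = 39 with acupuncture, and 18 + 3 = 21 in control.

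**2. The examples.** Three are defined by needling and cannot arise in a control patient: fainting during acupuncture treatment, and the two in "retained needle after treatment, and continuous severe pain more than one hour after acupuncture". Local hematoma and unbearable prickling are typical needling reactions. Pallor, sweating, dizziness and bleeding can occur in either arm. No stroke complication is named, although patients enter two to seven days after onset.

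**3. Effect of unequal capture.** The documents give no event rate and no capture probability, so every input here except 125 is an assumption. Let the true risk p be equal in both arms, and let capture be c1 with acupuncture and c0 in control. Observed risks are p × c1 and p × c0, so the observed risk ratio is c1 / c0, whatever p is.

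The chance of a nominally significant excess with acupuncture is approximately Φ[(p1 − p0 − 1.96 × s0) / s1]. Here p1 = p × c1, p0 = p × c0, s0 is the pooled standard error and s1 the unpooled one, each at 125 per arm.

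Example with p = 0.20 and capture 90% versus 60%: p1 = 0.18, p0 = 0.12, s0 = 0.0452 and s1 = 0.0450. Then (0.06 − 1.96 × 0.0452) / 0.0450 = −0.63, and Φ(−0.63) is about 26%.

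| Capture, acupuncture vs control | Observed risk ratio | Chance of a false excess: p = 10% | p = 20% | p = 30% |
|---|---|---|---|---|
| 90% vs 60% | 1.50 | 14% | 26% | 40% |
| 80% vs 60% | 1.33 | 9% | 15% | 21% |
| 90% vs 80% | 1.125 | 5% | 6% | 8% |
| 80% vs 80% | 1.00 | 2.5% | 2.5% | 2.5% |

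The last row is the nominal one-direction error of a two-sided 5% test.

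**The case against.** The strongest reply is that the written rule is the same in both arms. All adverse events are to be recorded, the list is only illustrative, and researcher observation at every visit does not depend on the patient volunteering anything. Severe cognitive impairment is excluded. Serious events go to the principal investigator at once, a Data and Safety Monitoring Board is in place, and scheduled NIHSS scoring would show neurological deterioration in either arm. Form-level detail, such as how observation is carried out, may sit in the operating procedures that the article mentions.

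Much of this stands, and it rules out several stronger readings:
- A reader might infer that patients who cannot speak are missed altogether. The second source and the cognitive exclusion do not support that. What remains is under-capture of subjective symptoms and of transient events between visits.
- A reader might count 21 contacts against 3 by setting aside the shared daily therapy. Both arms have that therapy, so 39 against 21 is the fairer count.
- A reader might take the examples as limiting what is recorded. The text says otherwise; they can only steer attention.
- A reader might take unequal capture as established. It is an inference from the design.

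The reply does not dispose of the point. The article does more than leave detail out: it states a passive method, in two sections, for a named outcome in a trial where patients and acupuncturists know the allocation.

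A further objection is that the stated safety analysis is narrower than all-cause incidence: "A safety analysis will be performed by analyzing the frequency of adverse events suspected as related to the treatment". That is a separate question about which recorded events are analysed. Changing it would not recover events that were never collected.

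**Conclusion.** The point holds as a risk of unequal ascertainment of unknown size. Collection by voluntary report and visit observation, with open allocation and 18 additional contacts in one arm, is likely to be less complete in controls. It is also likely to under-record subjective and between-visit events in patients with language deficits. If true risk is equal, the spurious ratio runs from 1 with equal capture, through about 1.1 at 90% versus 80%, to 1.5 at 90% versus 60%. These capture rates are assumptions, as are the true risks of 10% to 30% behind the error probabilities, and nothing in the article favours one over another. The contact count assumes that rehabilitation lasts the same three weeks as acupuncture. The primary outcome is not affected. The change is worth making because the trial sets out to evaluate safety and the remedy is cheap.

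**What to change.** In Secondary outcome measures and in Statistical analysis, base the between-arm incidence on one fixed set of adverse event questions:
- Ask them in both arms, with the same wording, at the visits already planned (week 1, week 3 and the final follow-up).
- Have existing trial staff other than the blinded outcome assessor ask them, for example the research nurses, who take no part in treatment. Answers about bleeding or hematoma could reveal allocation to the person scoring the NIHSS.
- Use the caregiver and the inpatient chart as sources when the patient cannot report.
- Cover general symptoms, stroke complications and death.
- Keep spontaneous reports for safety monitoring.
- Report needling-only events separately and descriptively for the acupuncture arm, outside the between-arm comparison.

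The cost is one case report form page and a few minutes at existing visits. Solicited questions raise reported counts in both arms. Because patients are unblinded, the change reduces differential reporting without removing it. Trial completion was expected by the end of June 2014, so patients already followed up would have been assessed under the passive method. A late change would mix two methods, and the report should state which applied to whom.
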